#### Baseline analyses

Baseline characteristics will be presented separately for children in the active and placebo groups using means and standard deviations for continuous data (or medians and interquartile ranges for non-normal data) and proportions for categorical data.

#### Primary outcome

The primary outcome (total score on the CYBOCS-PDD at 16 weeks) will be summarized by mean and standard deviation (SD) treatment group, with the comparison between active and placebo presented as the difference in means and the 95% confidence interval (CI), obtained using an unadjusted linear regression model. As a sensitivity analysis, the regression models will also be adjusted for pre-trial CYBOCS-PDD score, age, and IQ at baseline.

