**Methods/Design:**

The FAB study is a multicenter, double-blinded, randomized controlled trial, funded by the Australian Government’s National Health and Medical Research Council (NHMRC) grant. Participants will be aged between 7.5 and 17 years with a confirmed diagnosis of ASD. Eligible participants will be randomized to either placebo or fluoxetine for a 16-week period. Medication will be titrated over the first four weeks. Reponses to medication will be monitored fortnightly using the Clinical Global Impressions Scale (CGI). The primary outcome measure is the Children’s Yale-Brown Obsessive Compulsive Scale-Modified for Pervasive Developmental Disorders (CYBOCS-PDD), administered at baseline and 16 weeks. Secondary outcome measures include the Aberrant Behaviour Scale (ABC), the Spence Children’s Anxiety Scale Parent Report (SCAS-P), and the Repetitive Behaviors Scale (RBS-R), measured at baseline and 16 weeks. Participants will be invited to undergo genetic testing for *SLC6A4* allele variants using a cheek swab. Continuous outcomes, including the primary outcome will be compared between the active and placebo groups using unadjusted linear regression. Binary outcomes will be compared using unadjusted logistic regression.

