### Enrollment and randomization

After obtaining written consent from participants and/or their caregivers as per protocol guidelines, eligible participants will be randomized to the active or control group in a 1:1 ratio according to a computer-generated randomization schedule prepared by the Clinical Epidemiology and Biostatistics Unit (CEBU) at the Royal Children’s Hospital. Block randomization will be used with variable block sizes, with randomization stratified by site, age (7.5 to under 12 years and 12 to 17 years) and IQ (IQ ≥70: average or borderline range and IQ <70: intellectual disability). Thus there are a total of 12 strata (4 per site). The randomization schedule for each site will be given to the clinical trials pharmacist appointed at each site, who will then be responsible for arranging a sequential stock of trial medication for each stratum, labelled with only the study number, strata, and instructions for use. This schedule will remain confidential throughout the trial. The independent statistician from CEBU will also keep a copy of the master randomization schedule to check for any discrepancies. As each participant is enrolled in the study they will be allocated the next ID code within the correct stratum.

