#### Baseline and follow-up measures

The primary outcome measure (measured at baseline and 16 weeks) for the trial will be the Children*’*s Yale*-*Brown Obsessive Compulsion Scale*-*Modified for Pervasive Developmental Disorders (CYBOCS*-*PDD). The CYBOCS includes a detailed symptom checklist of possible obsessions and compulsions which are then rated across five severity items (time spent on obsessions, interference, distress, resistance, and degree of control) [20]. The CYBOCS has been modified for use in children with a pervasive developmental disorder (PPD). Both the CYBOCS-PDD and YBOCS (adult version) have been widely used in clinical drug trials for autism and have been demonstrated to be sensitive to change [13,21]. The CYBOCS-PDD score was chosen as the primary outcome measure for this trial, in line with previous trials in this field.

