#### Secondary outcomes

Secondary continuous outcomes will be compared between the active and control groups using unadjusted linear regression models, and binary outcomes using unadjusted logistic regression. As a sensitivity analysis regression models will also be fitted to the secondary outcomes adjusted for pretrial scores on the questionnaire of interest, age, and IQ at baseline (as used in the randomization).

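### The primary comparison of 16-week CYBOCS-PDD scores is unadjusted and the baseline-adjusted model is only a sensitivity analysis: a valid choice, but less precise than the collected data allow

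*Protocol article*

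**What the plan says.** The Primary outcome section takes the 16-week CYBOCS-PDD total score itself as the endpoint, not the change from baseline. The difference in means and its 95% confidence interval are "obtained using an unadjusted linear regression model". The section then adds: "As a sensitivity analysis, the regression models will also be adjusted for pre-trial CYBOCS-PDD score, age, and IQ at baseline".

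The Methods/Design paragraph of the abstract makes the same choice: "Continuous outcomes, including the primary outcome will be compared between the active and placebo groups using unadjusted linear regression". The Secondary outcomes section repeats it: "Secondary continuous outcomes will be compared between the active and control groups using unadjusted linear regression models". There too, a model with each scale's own pre-trial score, age and IQ is kept for sensitivity.

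Three other places bear on this:

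- **Baseline data.** Under Baseline and follow-up measures, and under Baseline, medical and genetic testing, CYBOCS-PDD and the continuous secondary scales (RBS-R, SCAS parent version, ABC) are all rated before randomization.
- **Stratification.** Enrollment and randomization describes variable blocks, "with randomization stratified by site, age (7.5 to under 12 years and 12 to 17 years) and IQ", giving 12 strata. Baseline CYBOCS-PDD is not a stratification factor.
- **Sample size.** The calculation uses an SD from a single time point, which is the right basis for an unadjusted comparison.

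The article gives no reason for ranking the unadjusted model first.

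**The concern.** A baseline score usually predicts a later score on the same scale. Leaving it out of the model puts predictable variation between participants into the error term, which widens the confidence interval and lowers power. It also means that a chance difference in baseline severity, which stratification by site, age and IQ does not control directly, is carried in part into the reported effect.

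Stratification is meant to remove variation between strata, but that gain is realized only if the factors enter the model. None of the three is in the primary model, and site is missing from the sensitivity model as well.

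The better model is already in the plan, but in second place. If the two results differ, the less precise one is the official finding. Reversing the order after unblinding would look selective.

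**Working it through.** **Inputs from the Sample size section.** Effect size 0.5 (2 points, SD 3.8; source SD 3.86), 80% power, two-sided alpha 0.05, 64 evaluable per group, 15% attrition, 73 recruited per group.

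**Assumed input.** The correlation r between baseline and 16-week CYBOCS-PDD. The article does not give it, so it is shown at 0.3, 0.5 and 0.7.

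**Step 1. The plan's own figure.** For a two-sample t-test at effect size 0.5, the required number is 63.77, so 64 per group. The normal approximation gives 63. The stated 64 is reproduced. Power at 64 per group is 80.1%.

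**Step 2. Effect of adding baseline.** Adjustment multiplies the residual SD by √(1 − r²), so the standardized effect becomes 0.5/√(1 − r²). The noncentrality with n per group is that effect times √(n/2). With n = 64, √32 = 5.657:

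| r | Variance removed (r²) | Standardized effect | Noncentrality | Power, 64 per group | Power, 62 per group |
|---|---|---|---|---|---|
| unadjusted | 0% | 0.500 | 2.83 | 80.1% | 78.9% |
| 0.3 | 9% | 0.524 | 2.97 | 83.7% | 82.5% |
| 0.5 | 25% | 0.577 | 3.27 | 90.0% | 89.0% |
| 0.7 | 51% | 0.700 | 3.96 | 97.6% | 97.2% |

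The last column uses 73 × 0.85 = 62.05 evaluable per group. These figures count the baseline score only. They give no credit for site, age and IQ, and they ignore the few degrees of freedom that covariates use.

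**Step 3. The same gain in other terms.** The evaluable number per group for 80% power is 64 unadjusted, and 59, 49 or 34 for the three values of r. With 64 per group and SD 3.8, the half-width of the 95% confidence interval is 1.33 points unadjusted, and 1.27, 1.15 or 0.95 points adjusted.

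**Step 4. Chance imbalance at baseline.** With 73 per group and SD 3.86, the standard error of the difference in baseline means is 3.86 × √(2/73) = 0.64 points. The 95% limit is 1.96 × 0.639 = 1.25 points. If the SD is the same at both times, the slope of the 16-week score on the baseline score is r, so a share r of an imbalance reaches the unadjusted estimate:

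- r = 0.3: 0.3 × 1.25 = 0.38 points
- r = 0.5: 0.5 × 1.25 = 0.63 points
- r = 0.7: 0.7 × 1.25 = 0.88 points

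The target difference is 2 points. An imbalance of one standard error (0.64) would shift the estimate by half as much or slightly more: 0.19, 0.32 or 0.45 points.

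**The case against.** The case for leaving the plan alone has real force.

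- **Validity.** Under 1:1 randomization the unadjusted difference is unbiased over repeated randomizations and holds its type I error. A reader might infer that the primary analysis is biased or wrong, but nothing in the article supports that. This point stands.
- **Consistency.** The trial was sized for an unadjusted comparison, and that is what it performs. A reader might infer that the choice leaves the trial underpowered. It does not: 64 evaluable per group gives 80.1%. The 78.9% at 62 per group comes from how attrition was allowed for, which is a separate matter, and with the 2-point difference and SD 3.86 taken literally, 62 per group still gives 81.7%. The power lost is power above the target.
- **Imbalance.** It is tempting to set the whole 1.25 points against the 2-point target. Only a share r passes through, and 1.25 is a limit exceeded about 5% of the time. The unadjusted confidence interval already allows for this variation, so imbalance and the wider interval are two views of one cost and should not be counted twice.
- **Transparency.** The adjusted model is specified in advance and baseline characteristics will be reported by group, so readers will see both.
- **Size.** The gain depends on r. At 0.3 it is under 4 percentage points of power, and the largest figures need r = 0.7.

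These arguments settle how serious the point is. They give no reason to prefer the less precise model, and they do not explain why site is absent from both models.

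**Conclusion.** The point holds as a weakness in efficiency and robustness. The unadjusted primary analysis is valid and agrees with the sample-size calculation, but it is less precise than an analysis the trial can run on data it already collects. At effect size 0.5 and 64 evaluable per group, the power forgone is about 4, 10 or 17 percentage points for r = 0.3, 0.5 or 0.7. The direction is secure for any non-trivial correlation. The size is not, because the article gives no r. The imbalance figures also assume equal SDs at the two times.

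This should be fixed, since it is a free improvement, but the trial's validity does not depend on it.

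**What to change.** Before unblinding:

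1. Define the primary analysis as a linear regression of 16-week CYBOCS-PDD on treatment, with baseline CYBOCS-PDD (continuous) and the stratification factors site, age and IQ as covariates. Report the adjusted difference with its 95% confidence interval.
2. Keep the unadjusted difference in means as a supportive analysis.
3. Do the same for RBS-R, SCAS parent version and ABC, each with its own baseline score.
4. Align the Methods/Design paragraph of the abstract, the Primary outcome section and the Secondary outcomes section, so that all three name the same primary model and site is included.

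The cost is a change of wording and a few degrees of freedom: with one term each for treatment, baseline score, age group and IQ group and two for site, the model has 7 parameters including the intercept instead of 2, so 128 participants leave 121 residual degrees of freedom instead of 126. This change needs no new data and no additional participants. The Trial status section says recruitment was still open when the article was submitted.

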#### Secondary outcomes

Secondary continuous outcomes will be compared between the active and control groups using unadjusted linear regression models, and binary outcomes using unadjusted logistic regression. As a sensitivity analysis regression models will also be fitted to the secondary outcomes adjusted for pretrial scores on the questionnaire of interest, age, and IQ at baseline (as used in the randomization).

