### Participants

Participants will need to meet eligibility criteria requirements in order to participate in the trial. Eligibility criteria for the study includes a confirmed diagnosis of ASD, based on the Autism Diagnostic Interview-Revised (ADI-R) and DSM-IV-TR [14,15], and aged between 7.5 and 17 years.

The presence of any exclusion criteria will preclude the participant from enrolling into the FAB study. Details of all participants deemed ineligible will be recorded. Exclusion criteria for the trial include a known DSM-IV diagnosis of Rett’s Disorder, Childhood Disintegrative Disorder, Schizophrenia or Major Depression. Patients currently prescribed or who have received in the previous six weeks prior to the trial other psychotropic medications, including other SSRI’s, typical and atypical anti- psychotics, mood stabilisers, and anxiolytic medication, monoamine oxidase inhibitor (MAOI) or pimozide, antidepressants, St John's Wort and/or atomoxetine will be excluded from the trial. Patients that have concomitant administration of drugs that interact with the metabolism of fluoxetine (such as phenytoin or carbamazepine) or drugs contraindicated for use with fluoxetine (such as monoamine oxidase inhibitors and pimozide) will be ineligible to take part in the study. Patients who have co-morbid significant medical conditions (such as unstable seizure disorder, cardiac disease, liver failure or renal failure) will not be eligible for the study. Female patients who are pregnant will not be allowed to participate in the study.

Stimulant medications were on the exclusion list of drugs for the Western Australian site (see site recruitment) only.

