### Site recruitment

The FAB trial will be conducted across three Australian sites: The Royal Children’s Hospital (Victoria), The Children’s Hospital at Westmead (New South Wales), and the State Child Development Centre (Western Australia).

Clinical sites were based on the likelihood of meeting recruitment goals and executing the protocol. All three centers care for similar numbers of children and adolescents with ASD. As such, it is thought that they will contribute equally to recruitment. Participants will be recruited through the following referral pathways: pediatricians, child and adolescent psychiatrists, psychologists, and general practitioners. Professionals who treat children and/or adolescents with autism at or around the above institutes will be sent a letter explaining the study, along with a study synopsis and copies of the study brochure for parents and/or guardians. Clinical trial coordinators will work together with clinicians who have been approached and are assisting with the study to ensure compliance with protocol guidelines and safety monitoring.

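### Site is a stratification factor but enters no planned model; if outcomes differ by site, linear-model intervals will be slightly too wide

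*Protocol article*

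**What the plan says.** Under Enrollment and randomization, participants are "randomized to the active or control group in a 1:1 ratio", with "randomization stratified by site, age (7.5 to under 12 years and 12 to 17 years) and IQ". The same section counts the cells: "Thus there are a total of 12 strata (4 per site".

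Under Primary outcome, the treatment difference and its interval are "obtained using an unadjusted linear regression model". The sensitivity model for that outcome is "adjusted for pre-trial CYBOCS-PDD score, age, and IQ at baseline". Under Secondary outcomes, the main models are again unadjusted (linear or logistic), and the sensitivity models are "adjusted for pretrial scores on the questionnaire of interest, age, and IQ at baseline (as used in the randomization". Site is in none of these models.

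Two other statements bear on site. Under Participants: "Stimulant medications were on the exclusion list of drugs for the Western Australian site (see site recruitment) only". Under Site recruitment, of the three centers: "it is thought that they will contribute equally to recruitment".

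**The concern.** Blocking within site forces the arms to be nearly balanced on site. If sites differ in outcome, that balance makes the treatment difference less variable than under simple randomization. A linear model without site does not know this: it leaves between-site variation in the residual and reports a standard error that is larger than the real sampling variability. The interval is then too wide, the test too conservative, and the precision gained by stratifying is partly thrown away.

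The article names its covariates and includes two of the three stratification factors, so the omission is a stated choice and not a detail left for later. Site is a credible prognostic factor because the sites recruit under different rules on stimulants. With roughly equal site shares, all three would contribute to the error term. The trial is sized for 80% power, so precision that costs nothing is worth keeping.

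**Working it through.** **The plan's own figure.** For effect size 0.5, 80% power and two-sided alpha 0.05, the normal approximation gives n = 2 × (1.960 + 0.842)² / 0.5² = 62.8, so 63 per group. The t-test solution is 63.8, so 64 per group, as stated under Sample size.

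**Inputs from the article.** Three sites, two age groups and two IQ groups (12 strata); 1:1 allocation; SD 3.8; difference of 2 points; 64 per group.

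**Input not in the article.** The share of outcome variance explained by site, R². Assumed range: 0% to 10%. For three equal-sized, equally spaced sites, the gap between the two extreme sites is 2 × 3.8 × √(1.5 × R²), which is 1.3, 2.1 and 2.9 points at 2%, 5% and 10%. The top of the range already exceeds the 2-point difference that the article calls clinically important.

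**Formulas.** SE without site: SE₀ = 3.8 × √(2/64) = 0.672. SE with site: SE₁ = SE₀ × √(1 − R²), which is also the true sampling SD when blocking balances site exactly. Type I error without site = 2 × [1 − Φ(1.96 × SE₀/SE₁)]. Power without site = Φ((2 − 1.96 × SE₀)/SE₁). Power with site = Φ(2/SE₁ − 1.96).

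| R² for site (assumed) | SE without site | SE with site | Ratio | Type I error without site | Power without site | Power with site |
|---|---|---|---|---|---|---|
| 0% | 0.672 | 0.672 | 1.000 | 5.0% | 84.6% | 84.6% |
| 2% | 0.672 | 0.665 | 1.010 | 4.8% | 84.8% | 85.3% |
| 5% | 0.672 | 0.655 | 1.026 | 4.4% | 85.2% | 86.3% |
| 10% | 0.672 | 0.637 | 1.054 | 3.9% | 85.8% | 88.1% |

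Power exceeds 80% in the first row because 2/3.8 = 0.526, not 0.5.

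**Simulation of the adjusted linear models.** 128 completers, 12 strata, variable blocks, 4,000 runs per scenario. Assumed: baseline score explains 25% of variance, age and IQ together 5%. The table gives the mean model SE divided by the true SD of the estimate (1.00 is correct), and the rejection rate under no treatment effect.

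| R² for site | Ratio without site | Ratio with site | Rejection without site | Rejection with site |
|---|---|---|---|---|
| 0% | 1.00 | 1.00 | 4.8% | 4.8% |
| 2% | 1.01 | 1.00 | 4.7% | 5.0% |
| 5% | 1.05 | 1.01 | 4.2% | 4.6% |
| 10% | 1.06 | 0.99 | 4.1% | 5.4% |

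The Monte Carlo standard error of a 5% rejection rate is √(0.05 × 0.95/4000) = 0.34 points, so the 2% row cannot be told from nominal. With no site effect, adding site moves the mean SE from 0.5637 to 0.5641, so an unnecessary site term is practically free.

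**Where most of the gain lies.** With site at 5% and a true difference of 2, simulated power was 85.3% unadjusted, 94.9% with baseline score, age and IQ, and 95.5% with site as well. Site adds 0.6 points; the other covariates add 9.6. The unadjusted model is also slightly conservative (ratio 1.02) with no site effect at all, because it omits age and IQ too.

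**Logistic models.** In 1,500 runs with an assumed true log odds ratio of 0.7 and a real site effect, adding site moved the mean log odds ratio from 0.64 to 0.72 and its mean SE from 0.361 to 0.387. The model without site was slightly conservative (0.361 against a true SD of 0.347), but adding site targets a conditional odds ratio and enlarges the SE.

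**The case against.** The strongest reply is that nothing here is invalid. Leaving out a stratification factor does not bias the linear treatment difference and does not inflate type I error. The models that come closest to the design are only sensitivity analyses. The loss depends on a site effect that the article neither states nor quantifies. That different people rate at each site is an inference: the article describes rater roles and supervision at each site but does not say so. All of this stands, and it is why the point is conditional and minor.

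A reader might go further and infer that standard errors are too large in every planned analysis. The article does not support that. With no site effect the adjusted linear model is correctly calibrated, and for the logistic models adding site raises the standard error.

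A reader might also infer that Secondary outcomes falsely claims to adjust for all the randomization factors. That is only one reading. The bracketed remark follows age and IQ and can mean that those two enter in their randomization categories. The list also contains the pretrial score, which is not a stratification factor, and the Primary outcome section carries no such remark. What remains under either reading is that site is omitted and the wording is ambiguous.

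**Conclusion.** The mismatch between the stratified design and the stated models is plain in the text. Its consequence is conditional. For the linear models, if site explains 2% to 10% of outcome variance, standard errors and intervals are about 1% to 6% too wide, type I error is about 4.8% to 3.9%, and about 0.5 to 2 points of power are lost. If sites do not differ, nothing is lost. The range is an assumption, and its upper end implies large differences between sites. For the unadjusted primary model, omitting the baseline score matters more than omitting site. Severity is minor and confidence moderate: the omission and its direction for linear models are certain, but its size in this trial is not known.

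**What to change.** - In Primary outcome and Secondary outcomes, add site as two indicator terms to the adjusted linear models, alongside baseline score, age and IQ.
- Make that design-matched model the main analysis for continuous outcomes and keep the unadjusted model as the sensitivity analysis. Fix this before unblinding; Trial status says that recruitment was still open at submission.
- Reword the bracketed remark so that it is accurate: name site, age and IQ as the stratification factors, and say whether age and IQ enter in their randomization categories. If site is deliberately left out, say why.
- For binary outcomes, site may be added for consistency with the design, with a note that the result is a conditional odds ratio and that its standard error will not shrink.

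Cost: a few words and two degrees of freedom. With 128 completers, the residual degrees of freedom go from 128 − 5 = 123 to 128 − 7 = 121.
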